## **Study Design and Duration**

*Study Design:* open-label, pre-/post-treatment study design.

A pilot study design was selected to investigate the effect of this particular BoNT A formulation on both IPD and ET when kinematic data is used to determine injection parameters. A control group is difficult for this study given that it would not be appropriate to inject individuals without tremor. Additionally, at this stage of the study, with very little published literature on this BoNT-A formulation, completing a randomized study between two BoNT A formulations

would not be reasonable. Instead, we have chosen to expose all participants to the same treatment.

Seventy participants will complete six injection cycles over 96 weeks. Participants will be allocated to one of two groups IPD (35 participants) or ET (35 participants) following assessment by a Movement Disorders Neurologist (MDN). To optimize BoNT A therapy efficacy, adjustments to injection site and units injected will be made as required later in the study based on benefit observed from previous injection cycles. Clinically judged improvement (by the MDN) and patient reported improvement will be the determinants of need for dose/injection site modification. If the first injection was sufficient in reducing tremor to an acceptable level, the same injection will be repeated. If not, then the injection parameters will be modified by the MDN. Routine clinical use of BoNT-A for tremor usually requires two consecutive injection cycles to optimize effect.

IPD participants will complete all visits in their optimal “on” state relative to their PD medications. Participants will be asked to take other medications as normal. They will be instructed not to ingest caffeine on the day of assessment to minimize confounding of tremor data. For all participants, the tremor dominant hand will be targeted for injection.

Xeomin® will be re-constituted by the same clinical nurse for all injections. This is done to ensure methodological consistency. To reduce bias, a single MDN will complete all injections for both groups. The MDN will determine parameters of injection using kinematic data for each injection course. The injecting MDN will be blinded to the kinematic/video recordings, but will make decisions from the analyzed data. Needle EMG may be utilized at the discretion of the MDN to ensure accuracy of injection sites in accordance with routine clinical practice. The injecting MDN will receive training in interpreting of kinematic data results prior to the initiation of the study.

*Duration:* Participants will receive a total of 6 injections and attend 13 study sessions over the course of 96 weeks. Duration of each participant visit will be approximately 75-90 minutes.

### **Total Number of Sites and Number of Canadian Sites**

*Total Number of Sites:* 1

*Number of Canadian Sites:* 1 (London Health Sciences Centre University Hospital, London, Ontario, Canada)

### **Sample Size**

*Number of subjects:* 70

*Sample size justification:*

|             |                               |
|-------------|-------------------------------|
| Alpha error | Alpha error = .05, two-sided. |
|-------------|-------------------------------|

|                                                  |                   |
|--------------------------------------------------|-------------------|
| Statistical power                                | $1-\beta = 0.95$  |
| Difference detectable with specified sample size | Effect size = .44 |

*Sample size calculations:* Power calculations are based on our previous pilot study as well as a review of relevant literature. We have based all power calculations at  $1-\beta = .95$  to ensure efficacy for the primary endpoint. Power calculations were conservatively based on *F*-test paradigm for ANCOVA using G\*Power 3.1.2 software package. Alpha error = .05.

There were no relevant studies on Xeomin® and hand tremor found in the literature search. To calculate effect size for efficacy of hand tremor management using Botulinum toxin A, we have used a randomized, double masked study of efficacy in essential tremor by Brin, et al. (2001). They calculated the effect size for  $N = 133$  (allocated to two groups high (100 units) and low (50 units)). For the current power calculation the low unit group was used as a conservative estimate. For tremor scale measures (primary endpoint) we used an effect size = .44 (Brin, et al. 2001). Based on previous studies in our group, we would anticipate a lower effect size for the kinematic outcome measures (secondary endpoint) estimated at .33 (overall tremor amplitude).

The target sample size for this study is  $N = 70$  (35 per group for both IPD and ET), which will allow for  $1-\beta = .95$  for an effect size for the primary endpoint of .44 and critical  $F = 3.98$ . This sample size will allow for an attrition rate of 20% while maintaining a  $1-\beta = .90$  ( $F = 4.02$ ) and an attrition rate of 37% while maintaining  $1-\beta = .80$  ( $F = 4.08$ ). Given the length of the study (5 visits over 8 months) we estimate a 30% attrition rate and have planned conservatively for that.

## Patient Population

*IPD:* botulinum toxin naïve consenting males and females, aged 18-80 years, diagnosed with stage H&Y 2-3 idiopathic Parkinson disease by the UK Brain Bank Criteria, with tremor as their primary and most bothersome symptoms, who have experienced a stable parkinsonian medication regime for at least 6 months prior to study enrolment.

*ET:* botulinum toxin naïve consenting males and females, aged 18-80 years, diagnosed with essential tremor by a qualified neurologist, presenting with tremor in their motor dominant hand, who have experienced a stable tremor medication regime for at least 6 months prior to study enrolment.

## Inclusion Criteria

1. Consenting male and female participants aged 18 years to 80 years
2. IPD: individuals diagnosed by UK Brain Bank Criteria with stage H&Y 2-3 idiopathic Parkinson disease (eligible only if tremor is the patient's primary and most bothersome symptom as determined by clinical exam and patient report)
3. ET: individuals diagnosed with ET presenting with hand tremor in their motor dominant hand
4. Stable IPD/ET medication management for 6 months prior to study enrolment
5. Individuals who are botulinum toxin naïve

## Exclusion Criteria

1. History of stroke
2. History of ALS or myasthenia gravis
3. Muscle weakness or any related compartmental muscle syndrome
4. Smoking
5. Offending medications (lithium, valproate, steroids, amiodarone, or beta-adrenergic agonists such as salbutamol)
6. Individuals prescribed zonisamide
7. History of allergic reaction to botulinum toxin or history of severe side effects in response to botulinum toxin injections
8. Contraindications per the Xeomin® drug monograph
9. Pregnant women

## **Drug Formulation**

*Drug formulation:* Single-use, sterile 100 Units lyophilized powder for reconstitution only with sterile, preservative-free 0.9% Sodium Chloride Injection, USP, prior to injection.

*Storage :* Unopened vials of XEOMIN can be stored at room temperature 20 to 25°C (68 to 77° F), in a refrigerator at 2 to 8°C (36 to 46°F), or a freezer at -20 to -10°C (-4 to 14°F) for up to 36 months. Do not use after the expiration date on the vial. Reconstituted XEOMIN should be stored in a refrigerator at 2 to 8°C (36 to 46°F) and administered within 24 hours.

*Safe Handling:* XEOMIN should not be used if the reconstituted solution has a cloudy appearance or contains floccular or particulate matter. Any reconstituted toxin solution for injection that has been stored for more than 24 hours, as well as any unused solution for injection, should be discarded.

## **Dosage Regimen**

100-300 units injected intramuscularly every 16 weeks.

*Rationale:* In clinic, injections are given every 12 weeks. To ensure complete wearing-off of drug effects before re-injection and prevent possible excess weakness, we have extended this period by 4 weeks.

*Drug Schedule:* Any changes to injection dosing or parameters will be based on kinematic measurements, though injection parameters will also be influenced by clinical outcome measures, as is the current standard clinical practice for Xeomin® injections.

## **Pre-Study Screening and Baseline Evaluation**

Patients are recruited by the principle investigator from his Movement Disorders Clinic at University Hospital, London, ON. Before enrolling the patient in the study, the patient's chart is examined to ensure validity for participation. No kinematic assessment, however, is carried out until the participants' first study visits.

## Treatment / Assessment Visits

Participants will be fitted with a hospital gown in order to allow full visibility of the limb under study. Participants are seated upright in a straight back chair with armrests. The tremor dominant arm is positioned on a supported armrest. A digital video recording device is statically positioned to capture a frontal view of the participant from the neck down. The laptop is positioned such that kinematic data is not observable to the participant during the study to avoid a bias or biofeedback effect.

Seven kinematic sensors (Noraxon, INC.) are used to collect data. An electrogoniometer with two degrees of freedom (DOF) is placed at the wrist to collect joint flexion-extension and ulnar-radial deviation information. Another electrogoniometer is placed at the elbow to measure flexion-extension movement and a final electrogoniometer is placed on the shoulder to measure flexion-extension and abduction-adduction movement information. A torsionmeter is placed on the underside of the forearm to collect wrist joint pronation-supination deviation information. Three tri-axial accelerometers are placed as follows: one at the distal joint of the third metacarpal, one on the back of the hand and one mid-forearm. The placement of these devices is standardized for each participant. Data recorded from the sensors is wirelessly transmitted to a signal receiver and laptop computer.

Study visits begin with a calibration stage. Calibration is used to determine baseline sensor location, as well as to confirm accuracy of sensor range for each degree of freedom (DOF). Each calibration position is maintained for 5 seconds. Each experimental task is repeated for three trials. Each trial position is maintained for duration of 20 seconds. A 30 second rest period is provided between each trial. Participants are instructed not to speak during recording to avoid confounding tremor data from accessory movement. The calibration and experimental tasks are described in Table 1.

*Table 1. Calibration and Experimental tasks*

| Calibration Tasks       |                                                                                                                                                                                           |
|-------------------------|-------------------------------------------------------------------------------------------------------------------------------------------------------------------------------------------|
| 1) 30° Flexion          |                                                                                                                                                                                           |
| 2) 30° Extension        |                                                                                                                                                                                           |
| 3) 30° Pronation        |                                                                                                                                                                                           |
| 4) 30° Supination       |                                                                                                                                                                                           |
| 5) 20° Ulnar deviation  |                                                                                                                                                                                           |
| 6) 20° Radial deviation |                                                                                                                                                                                           |
| Trial Tasks             |                                                                                                                                                                                           |
| 1) Supported Rest       | Participants rest their forearm in neutral position on a supportive armrest at mid-trunk height level                                                                                     |
| 2) Pronated Posture     | Participants fully extend their arms forward with hands in pronation at shoulder height level                                                                                             |
| 3) Neutral Posture      | Participants fully extend their arms forward with thumbs pointing upward at shoulder height level                                                                                         |
| 4) Kinetic              | Participants alternate touching fingertip to tip of a pen (held at arm's reach by a research associate) and their own nose                                                                |
| 5) Water Pouring        | Participants transfer water between two cups, one in each hand, keeping the transferring hand dynamic and the catching hand static. Distance between hands will be constant across trials |

|             |                                                                                                                                                                       |
|-------------|-----------------------------------------------------------------------------------------------------------------------------------------------------------------------|
| 6) Drinking | Participant will take a full cup of water and move the cup to mouth as if drinking                                                                                    |
| 7) Drawing  | Participants complete a variety of drawing tasks including Archimedes spirals and connecting two dots right-to-left and left-to-right on an electronic drawing tablet |

Non-kinematic outcome measures are collected at each visit. These include: measures of hand/finger strength to evaluate weakness secondary to Xeomin® injection (Manual Motor Testing and Excess Weakness Scale), measures of quality of life (QUEST), of motor function (Unified Parkinson Disease Rating Scale) and of tremor severity (Fahn-Tolosa-Marin Tremor Rating Scale).

### **Concomitant Medication**

*Concomitant medication:* Concomitant treatment of Xeomin® and aminoglycoside antibiotics, spectinomycin, or other agents that interfere with neuromuscular transmission (e.g., tubocurarine-like agents), or muscle relaxants, should be observed closely because the effect of Xeomin® may be potentiated.

*Drug interactions:* No formal drug interaction studies have been conducted with Xeomin®. Use of anticholinergic drugs after administration of Xeomin® may potentiate systemic anticholinergic effects. The effect of administering different botulinum toxin products at the same time or within several months of each other is unknown. Excessive neuromuscular weakness may be exacerbated by administration of another botulinum toxin prior to the resolution of the effects of a previously administered botulinum toxin. Excessive weakness may also be exaggerated by administration of a muscle relaxant before or after administration of Xeomin®.

*Contraindications:* Use in patients with a known hypersensitivity to the active substance botulinum neurotoxin type A, or to any of the excipients (human albumin, sucrose), could lead to a life-threatening allergic reaction. Xeomin® is contraindicated in patients with known hypersensitivity to any botulinum toxin preparation or to any of the components in the formulation. Use in patients with an infection at the injection site could lead to severe local or disseminated infection. Xeomin® is contraindicated in the presence of infection at the proposed injection site(s).

### **Rescue Medication & Risk Management**

*Rescue Medication:* Unfortunately, there is no rescue medicine able to reverse the effects of Xeomin®. However, the effects of the injection wear off in 2-3 months, though side effects such as weakness may wear off in as little as 2-3 weeks.

*Immunogenicity:* As with all therapeutic proteins, there is a potential for immunogenicity. The incidence of antibody formation is highly dependent on the sensitivity and specificity of the assay. In addition, the observed incidence of antibody positivity in an assay may be influenced by several factors including assay methodology, sample handling, timing of sample collection, concomitant medications, and underlying disease. For these reasons, comparison of the incidence of antibodies across products in this class may be misleading.

## Premature Withdrawal / Discontinuation Criteria

1. Withdrawal by Principle Investigator (PI) if PI feels continued participation would impair the participant's wellbeing.
2. Voluntary withdrawal by subject without prejudice to future treatment by the physician.

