## Safety Variables and Analysis

Any adverse reactions or events are handled in accordance with the University of Western Ontario Health Sciences Research Ethics Board's (HSREB) policy: patients are encouraged to seek emergency medical care if they feel they are experiencing an adverse reaction. We follow up with this patient in-hospital (if admitted) and after the incident. If the principle investigator feels that the health and/or safety of the patient would be compromised by continuing to participate in the study, the participant will be withdrawn. Any and all adverse events are reported to the HSREB and Merz Pharma Canada Ltd. (supplier of study drug).

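### Stopping injections has no status apart from leaving the study, and no closing assessment is named, so participants who leave mid-cycle may have no outcome for that cycle

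*Protocol*

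**What the plan says.** Premature Withdrawal / Discontinuation Criteria has two entries. One is "Withdrawal by Principle Investigator (PI) if PI feels continued participation would impair the participant's wellbeing". The other is "Voluntary withdrawal by subject without prejudice to future treatment by the physician". Discontinuation appears in the heading, but both entries describe withdrawal. Safety Variables and Analysis follows the same line: if the investigator judges that health or safety would be compromised, "the participant will be withdrawn". The only follow-up described there is contact after an adverse reaction: "We follow up with this patient in-hospital (if admitted) and after the incident". It names no tremor, kinematic or strength measure.

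Treatment / Assessment Visits ties outcome collection, including the FTM scale and the strength measures, to study visits.

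Study Design and Duration sets the schedule: "Seventy participants will complete six injection cycles over 96 weeks", with 13 sessions in all. Dosage Regimen puts injections 16 weeks apart. Rescue Medication & Risk Management says that "the effects of the injection wear off in 2-3 months" and that side effects such as weakness may resolve in as little as two to three weeks.

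Sample Size expects substantial loss, on a different schedule: "Given the length of the study (5 visits over 8 months) we estimate a 30% attrition rate".

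**The concern.** Stopping treatment and ending data collection are separate events, and the Protocol provides only for both together. Once injections stop, nothing asks the participant to come back for a score, although the last injection may still be acting.

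The design makes this matter. It is open-label with no control arm, and the efficacy claim is a change from before to after injection. No second arm would show that selective loss is shifting the result. If those who leave tend to be those with little benefit or with troublesome weakness, the remaining data overstate improvement and understate weakness. Research question iii is exposed too: it compares baseline tremor composition between participants with more than 8 points of change and those with 8 or fewer, and selective loss would thin the second group.

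A statistical analysis plan can choose how to handle missing scores. It cannot recover scores that were never collected. Who is asked to return, and for which measurements, is a matter of protocol conduct.

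**Working it through.** **1. How the Protocol treats attrition: the power figures.** Inputs from Sample Size: effect size 0.44 (taken as Cohen's f), alpha 0.05, two groups, N = 70. One covariate is assumed. The method is the noncentral F test for ANCOVA with numerator df 1, denominator df N − 3 and noncentrality f² × N = 0.1936 × N.

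| Loss | N | f² × N | Critical F (stated) | Power (stated) |
|---|---|---|---|---|
| 0% | 70 | 13.55 | 3.98 (3.98) | 0.952 (0.95) |
| 20% | 56 | 10.84 | 4.02 (4.02) | 0.898 (0.90) |
| 37% | 44 | 8.52 | 4.08 (4.08) | 0.813 (0.80) |
| 30% | 49 | 9.49 | 4.05 (none) | 0.854 (none) |

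The stated figures reproduce. On its own terms the plan covers a 30% loss for power. That says nothing about which participants are lost.

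**2. Whether 30% fits this trial.** It is given for five visits in eight months; the trial has 13 sessions in 96 weeks. Suppose, as an assumption, that the same dropout rate continues:
- counting 96 weeks as three such periods: 70 × 0.7³ = 24.0 remain;
- taking eight months as 34.8 weeks: 70 × 0.7^(96/34.8) = 26.2 remain.

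So 24 to 26 participants would remain, a loss of 63–66% (1 − 26/70 to 1 − 24/70), with power of 0.54 to 0.58 by the same formula. This shows only that loss could exceed 30%; it is not a forecast.

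**3. Who lacks an outcome.** Thirteen sessions for six injections fit one baseline plus two per cycle: 1 + 2 × 6 = 13. This is inferred, not stated. On that reading:
- a participant who leaves after the within-cycle sessions has a score for that cycle;
- a participant who leaves before them has none for that cycle;
- both keep their scores from earlier cycles;
- neither has scores for later time points.

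Later contact is a poor substitute, because weakness may resolve within weeks and the injection effect within two to three months.

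**4. How wide the uncertainty could be.** Leavers at 30%: 0.30 × 70 = 21; completers: 49. Assume that 24 of 49 completers respond (49%) and that no leaver has a usable outcome.
- No leaver responds: 24/70 = 34%.
- Every leaver responds: (24 + 21)/70 = 45/70 = 64%.

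The responder count is assumed, and the range is a worst case. Each leaver with a usable score narrows it.

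**The case against.** The case on the other side has real force.

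- **Many leavers will have been scored.** Outcomes are taken at every visit, and someone who declines the next injection at the end of a cycle has probably been assessed for the cycle just finished. A reader might infer that everyone who drops out lacks an outcome for the last cycle. The schedule does not support that; it applies to those who leave mid-cycle.
- **The analysis may use partial data.** A reader might infer that the efficacy result will describe only participants who stay. That depends on the analysis set, the missing-data method and the endpoint visit. The analysis flow charts are not visible, and a statistical analysis plan may settle these points. Selection is therefore a risk, not an established property of the analysis.
- **Poor response has another route.** Study Design and Duration lets injection parameters be modified when the first result is insufficient, so lack of benefit need not mean leaving. That weakens any claim about who will leave. It does not cover weakness or withdrawal by the investigator.
- **The text does not forbid later assessment.** It is silent, and the consent pages are not at hand. But the Protocol is the document that site staff follow, and it describes no status other than withdrawal.
- **This is a single-site pilot.** That limits how much machinery is reasonable, but the remedy mostly uses sessions that already exist.

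What stands is the gap in data collection.

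**Conclusion.** The point holds as a design weakness that should be corrected. It does not invalidate the trial. The Protocol gives no way to stop injections and remain under assessment, and names no closing assessment. Mid-cycle leavers may lose that cycle's outcome and will lose later ones. Loss related to poor response or weakness would bias the result in the favourable direction, with no control arm to reveal it.

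The size of that bias cannot be derived from the document. The 34% to 64% range shows what is at stake under stated assumptions: 30% loss, 24 of 49 completers responding, and no usable outcome for the 21 leavers. A reader might want to go further and put a figure on the inflated mean change, for instance by giving leavers no improvement. The Protocol supplies no basis for leavers' scores, and that exercise would also discard the scores they gave before leaving.

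Nor should 30% be read as the expected loss for this trial. It belongs to a schedule that contradicts the one in Study Design and Duration, and the two must be reconciled. The power arithmetic is sound for the inputs stated; the issue is bias.

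**What to change.** In Premature Withdrawal / Discontinuation Criteria, define stopping injections and withdrawing consent as separate events. Ask participants who stop injections, by their own or the investigator's decision, but do not withdraw consent, to attend the remaining scheduled sessions of their current 16-week cycle. If they will not attend all of them, ask for one closing visit. Collect the full FTM, kinematic and strength set each time. The reasons for stopping treatment stay as they are, and participants remain free to decline.

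State that these scores, and all earlier post-injection scores, enter the primary analysis of everyone injected. The handling of scores that are still missing can be left to the statistical analysis plan.

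In Sample Size, reconcile the visit count and duration behind the 30% with 13 sessions in 96 weeks, and restate expected attrition on that basis.

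The cost is amendment wording and a few mostly already scheduled visits for people no longer being treated. The result may be less favourable.
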